## GLOSSARY OF ABBREVIATIONS

|      |                                |
|------|--------------------------------|
| BP   | Blood pressure                 |
| FSH  | Follicle stimulating hormone   |
| GnRH | Gonadotropin releasing hormone |
| HA   | Hypothalamic amenorrhoea       |
| HPG  | Hypothalamic-pituitary-gonadal |
| HR   | Heart rate                     |
| IN   | Intranasal                     |
| KP54 | Kisspeptin-54                  |
| LH   | Luteinising hormone            |

## KEYWORDS

Kisspeptin, fertility, neuropeptides, reproduction, neuroendocrinology, intranasal.

## STUDY SUMMARY

|                         |                                                                                                                                                                                                                                                                                                                       |
|-------------------------|-----------------------------------------------------------------------------------------------------------------------------------------------------------------------------------------------------------------------------------------------------------------------------------------------------------------------|
| TITLE            | Investigating the Effects of Intranasal Kisspeptin Administration on Reproductive Hormone Secretion.                                                                                                                                                                                                                  |
| DESIGN           | Randomised, double-blind, placebo-controlled, crossover study comparing intranasal kisspeptin administration versus intranasal placebo on reproductive hormone release in humans.                                                                                                                                     |
| AIMS             | To investigate the effects of intranasal kisspeptin administration on reproductive hormone release in healthy volunteers (men and women) and female patients with reproductive disorders (including hypothalamic amenorrhoea).                                                                                 |
| OUTCOME MEASURES | Blood levels of reproductive hormones measured using automated chemiluminescent immunoassays at baseline and every 15 minutes for 4 hours. Safety monitoring: heart rate, blood pressure, and the presence of adverse symptoms measured using automated blood pressure monitor every 15 minutes for 4 hours           |
| POPULATION       | A minimum of 12 healthy volunteers (i.e., healthy men and healthy women) and 6 patients with reproductive disorders.                                                                                                                                                                                                  |
| ELIGIBILITY      | Healthy volunteers (with normal reproductive function [men and women], including regular menstrual cycles and not taking hormonal contraception [women]). Patients with reproductive disorders, diagnosed in accordance with established guidelines (e.g. Endocrine Society guidelines for hypothalamic amenorrhoea). |
| DURATION         | Recruitment will stop when sufficient participant numbers have been enrolled to ensure the planned sample size has been achieved. The study will stop once all participants have completed the study protocol.                                                                                                        |

## 1. INTRODUCTION

### 1.1. BACKGROUND

Reproductive disorders encompass a broad range of highly prevalent conditions, frequently caused by aberrations in the hypothalamic-pituitary-gonadal (HPG) reproductive axis. Indeed, recent epidemiological data highlights that infertility is experienced by 12.5% of women and 10.1% of men in the United Kingdom (1). Despite the major health burden associated with reproductive disorders, many standard therapies are limited by poor efficacy, contraindicated in many, and carry significant side-effects. Hence, novel, safe, and effective clinical strategies are therefore much-needed.

The reproductive neuropeptide kisspeptin has emerged as critical for mammalian reproduction due to its key role as an upstream regulator of gonadotropin-releasing hormone (GnRH) secretion. This in turn controls downstream gonadal function via the gonadotropins luteinising hormone (LH) and follicle-stimulating hormone (FSH). As such, due to kisspeptin's key role in regulating physiological reproductive hormone secretion, there has been accumulating clinical and research interest in using kisspeptin-based medicines to restore hormonal secretion in common reproductive disorders, including hypothalamic amenorrhea (HA) (2–4), hyperprolactinemia (5, 6), type 2 diabetes and obesity-related hypogonadism (7), and as a safer trigger for inducing oocyte maturation in *in vitro* fertilization (8–10).

However, current administration of kisspeptin is confined to the invasive subcutaneous or intravenous routes which limits patient acceptability and clinical use. Therefore, alternative delivery routes could overcome this and further accelerate the development of kisspeptin-based therapeutics in humans. To this end, the aim of this study is to investigate the effects of intranasal kisspeptin administration on reproductive hormone release in humans.

### 1.2. RATIONALE FOR CURRENT STUDY

This study is designed to investigate the effects of intranasal kisspeptin administration on reproductive hormone release in healthy volunteers (men and women) and female patients with reproductive disorders (such as HA). Participants will attend for at least two study visits each comparing intranasal kisspeptin administration versus intranasal placebo, as part of a randomised, double-blind, placebo-controlled, crossover study. Following self-administration of intranasal kisspeptin or placebo (using a nasal spray device), serum reproductive hormones will be measured every 15 minutes for 4 hours.

**Primary Hypothesis:** Intranasal kisspeptin administration stimulates reproductive hormone secretion in healthy volunteers and patients with common reproductive disorders.

## 2. STUDY OBJECTIVES

### Primary Outcome:

Change in serum LH following intranasal administration of kisspeptin compared to placebo. Blood samples will be taken at baseline (pre-administration) and every 15 minutes for 4 hours.

## Secondary Outcomes:

1. Change in serum FSH following intranasal administration of kisspeptin compared to placebo. Blood samples will be taken at baseline (pre-administration) and every 15 minutes for 4 hours.
2. [Men]: Change in serum testosterone following intranasal administration of kisspeptin compared to placebo. Measurements will be taken at baseline (pre-administration) and every 15 minutes for 4 hours.
3. [Women]: Change in serum oestradiol following intranasal administration of kisspeptin compared to placebo. Measurements will be taken at baseline (pre-administration) and every 15 minutes for 4 hours.
4. [Women]: Change in serum progesterone following intranasal administration of kisspeptin compared to placebo. Measurements will be taken at baseline (pre-administration) and every 15 minutes for 4 hours.
5. Safety assessments: standard adverse event reporting, blood pressure, and heart rate recordings.

## 3. STUDY DESIGN

This is a randomised, double-blind, placebo-controlled, crossover study investigating the effects of intranasal kisspeptin administration on reproductive hormone release in healthy volunteers (men and women) and patients with reproductive disorders. The cross-over design has been chosen as it is the most rigorous method to determine a treatment effect, by minimising the effect of confounding variables. Each participant will be required to attend all study visits, hence serving as their own control.

**The study will recruit three groups of participants.** *Group A* will consist of healthy men with normal reproductive function and will also determine the optimal dose for intranasal kisspeptin administration. *Group B* will consist of healthy (ovulatory) women with normal reproductive function. *Group C* will consist of female patients with reduced reproductive function, such as HA. The groups will not be recruited in parallel, as the results from *Group A* will determine the optimal dosing for *Groups B* and *Groups C*.

### Participants

A minimum of 12 healthy volunteers (*Group A* and *Group B*) and 6 patients with reproductive disorders (*Group C*) will be recruited (described in Section 4).

### Pre-Study Visits

Recruited participants will be asked to abstain from alcohol, caffeine, and sexual activities from 22:00 before their study visits and to consume a normal breakfast on their study days. All study visits will start in the morning to control for circadian hormonal changes. Study visits for participants in *Group A* and participants in *Group C* (e.g., anovulatory women) will take place at least 1 week apart (to ensure washout). Study visits for participants in *Group B* will take place during the follicular phase of the menstrual cycle, i.e., days 2-10 inclusive (to control for reproductive hormone changes over the menstrual cycle).

### Study Visits

Study visits will take place at the Clinical Research Unit (Imperial College Healthcare NHS Trust) and all participants within each group will receive the same protocol during each study visit.

**Group A (Healthy Men):** Kisspeptin has not been administered via the intranasal route to humans and thus this part of the study will also determine the optimal dosing protocol for intranasal kisspeptin delivery. Participants will attend for five study visits each and will receive the following five interventions (on separate visits and in random order) via the intranasal route: 3.2, 6.4, 12.8, and 25.6 nmol/kg of kisspeptin-54, and 0.9% saline (placebo). After self-administration of kisspeptin-54 or placebo at timepoint 0 minutes, serum levels of LH, FSH, and testosterone will be measured every 15 minutes for 4 hours (**see Figure 1**).

**Figure 1 – Protocol Schematic (Group A)**

[figure not shown]

**Group B (Healthy Women):** Participants will attend for two study visits each, receiving kisspeptin-54 and 0.9% saline (placebo) (on separate visits and in random order) via the intranasal route. The dose of kisspeptin-54 will be determined based on the results of Group A, i.e., the dose of kisspeptin-54 which elicits the greatest maximal increase in serum LH in healthy men. After self-administration of kisspeptin-54 or placebo at timepoint 0 minutes, serum levels of LH, FSH, oestradiol, and progesterone will be measured every 15 minutes for 4 hours (**see Figure 2**).

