**Figure 2 – Protocol Schematic (Group B)**

[figure not shown]

**Group C (Female patients with Reproductive Disorders):** Patients will attend for two study visits each, receiving kisspeptin-54 and 0.9% saline (placebo) (on separate visits and in

random order) via the intranasal route. The dose of kisspeptin-54 will be determined based on the results of *Group A* (described above) and will be the same dose examined in *Group B*. After self-administration of kisspeptin-54 or placebo at timepoint 0 minutes, serum levels of LH, FSH, oestradiol, and progesterone will be measured every 15 minutes for 4 hours (**see Figure 3**).

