### **Safety of participants during the Study**

Participants will remain in the investigation unit for a short period of observation after termination of the study visit. At least two clinically trained investigators will be present throughout each study visit. During the study, blood pressure, and heart rate measurements will be taken at 15-minute intervals. Participants will be encouraged to report any unusual or unpleasant sensation to the investigators immediately. Any significant adverse effects will lead to withdrawal of the individual and any serious adverse effects will terminate the whole study.

Throughout the study there will be at least one physician available 24 hours per day via a direct line, with a second physician on back up, and a secondary direct line to one of the senior physicians. Although we do not anticipate any serious adverse effects, participants will be provided with contact numbers and clear instructions that, if they feel unwell, they should call us. Kisspeptin is rapidly cleared (11, 12) and participants would not be anticipated to experience any delayed effects on completion of the study visit.

The Chief Investigators, [name] and [name], are on site, and any potential side-effects of the study will be reviewed regularly by [name] and [name] and the other main investigator for the study ([name]). The safety of the participants is of the highest importance throughout the study. An internal audit will be completed at the end of the study. Study efficacy and safety will be regularly reviewed in fortnightly meetings. A formal data monitoring committee is not necessary as kisspeptin has been given to over 500 human subjects and is safe and well tolerated. The study may be subject to audit by Imperial College London under their remit as sponsor and other regulatory bodies to ensure adherence to GCP and the UK Policy Framework for Health and Social Care Research.

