### **Kisspeptin**

Kisspeptin is a naturally occurring and safe hormone, which is known to play a critical physiological role in human fertility (13, 14). Kisspeptin has been given safely to over 500 male and female participants in subcutaneous and intravenous form without side effects (15–18). Levels of kisspeptin in the circulation increase ~7,000-fold during normal pregnancy without any known adverse effects (19). We do not anticipate any adverse effects of the doses of kisspeptin proposed in the study, however if any serious adverse effects are noted at any time, we will immediately suspend the study, report to the sponsor and review continuation of the research with the research ethics committee. The intravenous half-life of kisspeptin is short (28 minutes) and if any unexpected adverse effects are encountered (not expected), we would expect these to resolve rapidly with supportive management.

Kisspeptin-54 is stored at -20°C as per manufacturer's guidelines. Freeze-dried kisspeptin-54 vials will be reconstituted on the morning of each study visit to produce a solution containing the target dose, which will be self-administered by the participant (under supervision of the clinical team) using a nasal spray device

The maximum doses of kisspeptin-54 administered will be 25.6nmol/kg. We have already administered these identical doses during our previous studies (8, 15, 16, 20) that have demonstrated to safely produce a biological effect without untoward side effects. Intranasal placebo administration will consist of saline (identical in volume and appearance to kisspeptin), thus respecting the study's double blinded design.

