#### 4.3. WITHDRAWAL CRITERIA

If a participant loses capacity during the study, then they would be withdrawn from further participation in the study. However, any data or samples that we had already collected when they were able to give consent would be used in the study. We will seek their informed written consent for this at the screening visit. If consent is not given to this and the participant loses capacity, samples would be disposed of in accordance with the Human Tissue Authority's Code of Practice following completion of the study and not kept for use in future ethically approved research.

Any significant adverse effects will lead to withdrawal of the individual and any serious adverse effects will terminate the whole study.

It will be made clear to participants that they will be free to withdraw from the study at any time without providing any reason.

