## 5. ADVERSE EVENTS

#### 5.1. DEFINITIONS

**Adverse Event (AE):** any untoward medical occurrence in a patient or clinical study subject.

**Serious Adverse Event (SAE):** any untoward medical occurrence or effect that:

- **Results in death**
- **Is life-threatening** – *refers to an event in which the subject was at risk of death at the time of the event; it does not refer to an event which hypothetically might have caused death if it were more severe*
- **Requires hospitalisation, or prolongation of existing inpatients' hospitalisation**
- **Results in persistent or significant disability or incapacity**
- **Is a congenital anomaly or birth defect**

Medical judgement should be exercised in deciding whether an AE is serious in other situations. Important AEs that are not immediately life-threatening or do not result in death or hospitalisation but may jeopardise the subject or may require intervention to prevent one of the other outcomes listed in the definition above, should also be considered serious.

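### The dose for Groups B and C is chosen on the LH peak alone; the tolerability recorded at each Group A dose has no stated bearing on it

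*Protocol*

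**What the plan says.** Group A (healthy men) receives four intranasal doses of kisspeptin-54 (3.2, 6.4, 12.8 and 25.6 nmol/kg) and saline, on separate visits in random order. Its results set the dose for the later groups, which are not recruited in parallel with it (Protocol Section 3, Study Design and Study Visits).

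- **Rule for Group B:** "the dose of kisspeptin-54 which elicits the greatest maximal increase in serum LH in healthy men". The protocol introduces this with an i.e., so it defines the dose and is not an example.
- **Rule for Group C:** the dose comes from Group A "and will be the same dose examined in" Group B.
- **Novelty:** "Kisspeptin has not been administered via the intranasal route to humans" (Study Visits). The safety record cited under Kisspeptin was obtained "in subcutaneous and intravenous form without side effects".
- **Data collected:** heart rate, blood pressure and adverse symptoms every 15 minutes at every visit.
- **Safeguards:** "Any significant adverse effects will lead to withdrawal of the individual and any serious adverse effects will terminate the whole study" (Section 4.3, and also under Safety of participants). The Kisspeptin subsection provides for suspension and ethics review after a serious effect. Section 5.1 also counts as serious an important event that "may jeopardise the subject or may require intervention to prevent one of the other outcomes". In addition, "any potential side-effects of the study will be reviewed regularly", and "Study efficacy and safety will be regularly reviewed in fortnightly meetings".

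**The concern.** Group A is the protocol's only source of intranasal tolerability data before healthy women and patients are dosed. Those data are collected at every dose, but the sentence that turns Group A results into a dose uses only the LH peak. Read as written, a dose at which several men were withdrawn for significant but non-serious effects would still go forward if its LH peak were the largest, by whatever margin. A better tolerated dose with nearly the same LH response would be passed over.

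This is not a detail that a protocol commonly leaves to the statistical analysis plan. The protocol itself fixes the rule, and the rule decides what later participants receive.

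**Working it through.** **Step 1: does any other text condition the dose choice?**

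| Provision | Acts on | Stated effect on the dose |
|---|---|---|
| Dose sentence, Group B (carried to Group C) | Dose | LH peak only |
| Optimal dosing, Study Design and Group A text | Dose | None beyond the Group B definition |
| Serious effects: termination or suspension | Whole study | None |
| Significant effects: withdrawal | That individual | None |
| Regular side-effect review, fortnightly meetings | Study oversight | None stated |

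The uncovered area is therefore intolerance that is significant enough for withdrawal but not serious. The broad definition in Section 5.1 makes that area smaller still.

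**Step 2: number of men.** Section 7 gives 10 per group, raised to 12 for dropout. A two-sided paired t-test with effect size 0.997, alpha 0.05 and power 0.80 needs n = 9.98, so 10, and 10 × 1.2 = 12. Both figures reproduce. The Participants paragraph gives a minimum of 12 healthy volunteers for Groups A and B. If that means both groups together, Group A could have 6 men, so 6 is shown as a low case.

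**Step 3: what a withdrawal criterion would do.** Take the criterion that a dose is excluded if two or more men are withdrawn at it for significant adverse effects. For n men at a dose and true withdrawal rate p:

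P(excluded) = 1 − (1 − p)^n − n·p·(1 − p)^(n − 1)

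Example, n = 10 and p = 0.02: 1 − 0.8171 − 0.1667 = 0.016.

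| Assumed p | n = 6 | n = 10 | n = 12 |
|---|---|---|---|
| 2% | 0.6% | 1.6% | 2.3% |
| 10% | 11.4% | 26.4% | 34.1% |
| 20% | 34.5% | 62.4% | 72.5% |
| 30% | 58.0% | 85.1% | 91.5% |

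Every p is an assumption, because the documents give no intranasal event rates. The formula also assumes that each man receives each dose. A man withdrawn at one visit misses his later doses, so the number per dose would be somewhat lower and the exclusion chances with it.

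**The case against.** **The harm is small and the rule is coherent.** This stands. LH is the primary outcome, so choosing by LH is sensible. Each participant in Groups B and C receives one supervised active dose. The kisspeptin-versus-placebo comparison stays valid at whichever dose is chosen, because each participant is her own control.

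**Oversight makes the bad outcome unlikely.** This stands in part. The chief investigators review side-effects and hold the randomisation sequence, and the groups are sequential, so a by-dose look before Group B is feasible. But no provision says that the look may change the dose. Preferring a better tolerated dose would mean departing from the stated rule or amending it, after efficacy and safety are known.

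**The doses have been used before.** The Kisspeptin subsection says that identical doses were given in earlier studies without untoward effects. Since intranasal use is stated to be new, that experience came by other routes and does not settle nasal tolerability. It is also true that the protocol gives no reason to expect tolerability to differ across the four doses.

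**A sentence requiring that by-dose safety be considered would be enough.** That would help, but it leaves the choice to discretion. A limit tied to the protocol's own withdrawal rule costs no more.

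**A symptom-count limit might look like a natural addition.** It is not recommended. Suppose a dose were excluded when at least 3 more men had symptoms on it than on saline. With 10 to 12 men, at least one of four harmless doses would be excluded in 11–15% of trials if 10% of men had symptoms on saline, and in 24–28% if 20% did. Trivial, transient symptoms could then remove the most effective dose.

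**Conclusion.** The point holds as a limited gap in a stated rule. The LH peak alone selects the dose for Groups B and C, and the intranasal tolerability data from Group A have no stated effect. The change should be made because it protects participants and costs almost nothing, but the consequence is modest and confined to significant, non-serious intolerance.

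A reader might infer that the protocol lets an unsafe dose go forward unchecked. The documents do not support that: serious effects end or suspend the study, important events that may need intervention count as serious, and safety is reviewed every fortnight. A reader might also infer that the rule is likely to pick a poorly tolerated dose. That cannot be shown either, because no intranasal event rates or dose-response are given. The percentages in the working describe the proposed criterion under assumed rates and do not measure harm from the current text.

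**What to change.** In the Group B text of Section 3, keep "the dose of kisspeptin-54 which elicits the greatest maximal increase in serum LH in healthy men" and add: among doses at which no more than one man was withdrawn for significant adverse effects. Carry the same wording to Group C. State that the chief investigators, who hold the randomisation sequence and take no part in visits or data analysis, apply this in a documented by-dose safety review after the last Group A visit and before Group B opens, and pass on only the chosen dose. Add that Group B does not open without an amendment if no dose qualifies.

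The cost is one clause and one by-dose table of data already collected. Little or no delay follows, since the groups are already sequential and the LH results must be read by dose anyway. Sample size and endpoints do not change. The downside is a slightly less simple rule and, with 10 to 12 men and an assumed 2% true withdrawal rate, about a 2% chance per dose of excluding an acceptable one. In that case the next-best LH dose would be used. With only 6 men the criterion would detect poor tolerability much less often.
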